**Methods:**

The ASEPTIC trial is a multicentre, placebo-controlled, double-blinded, randomised controlled trial (RCT) in England, Scotland, and Wales. Patients aged 18 years and older with cirrhosis and ascites requiring diuretic treatment or paracentesis, and no current or previous episodes of SBP, are eligible, subject to exclusion criteria. The trial aims to recruit 432 patients from at least 30 sites. Patients will be randomised in a 1:1 ratio to receive either oral co-trimoxazole 960 mg or an identical placebo once daily for 18 months, with 6 monthly follow-up visits thereafter (with a maximum possible follow-up period of 48 months, and a minimum of 18 months). The primary outcome is overall survival. Secondary outcomes include the time to the first incidence of SBP, hospital admission rates, incidence of other infections (including *Clostridium difficile*) and antimicrobial resistance, patients’ health-related quality of life, health and social care resource use, incidence of cirrhosis-related decompensation events, liver transplantation, and treatment-related serious adverse events.

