#### Sample size {14}

For overall survival as the primary outcome, we anticipate a hazard ratio (HR) of 0.62 and calculated that 432 patients will be required to generate 187 events, incorporating a 10% cumulative probability of loss-to-follow-up by the end of the study. Guided by the Kaplan–Meier 18-month survival estimate amongst patients with cirrhosis and ascites in the control arm of the ANSWER trial [30], and assuming an exponential survival distribution, we anticipate 66% survival in the control arm at 18 months. In the experimental arm, we expect 77% of patients surviving at 18 months. The recruitment will be uniform over a period of 2.5 years, and the follow-up time will be 18 months minimum with a maximum potential follow-up of 48 months. This calculation was based on a two-sided 5% type 1 error rate and 90% power. The primary event rate overall (blinded to allocation) will be monitored by the trial steering committee, and follow-up may be extended beyond the planned period to achieve the required number of events, with any extension agreed with the funder. Disruption to the trial schedule owing to the COVID-19 pandemic may necessitate an extension of the recruitment period.

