## Statistical methods

### Statistical methods for primary and secondary outcomes {20a}

A detailed statistical analysis plan will be written prior to the first unblinded analysis and approved in advance by the trial steering committee. The main analyses will be conducted following the intention-to-treat principle. For the primary outcome, Kaplan–Meier survival curves will be compared using the log-rank test, according to the allocated treatment in an intention-to-treat manner. An unadjusted Cox proportional hazards model will be fitted, and the unadjusted hazard ratio and 95% confidence interval will be presented. An adjusted Cox model will then be fitted, adjusting for the stratification factors (active participation on the liver transplant waiting list, rifaximin prescription at enrolment, alcohol as a cause of cirrhosis, and active alcohol consumption at randomisation if the amendment submitted in June 2022 is successful) by including them as covariates in the model. All statistical tests will use a two-sided *p*-value of 0.05.

If there is evidence of non-proportional hazards, the life expectancy difference and life expectancy ratio between the two arms will be presented [36]. The stratified log-rank test will be reported in this instance as well, and the odds ratio for death at 18 months will be calculated using logistic regression.

Binary secondary outcomes will be analysed using logistic regression, and continuous outcomes using linear regression adjusting for baseline values (i.e. ANCOVA). Time to the first incidence of SBP will be presented with Kaplan–Meier curves and compared between the arms using the log-rank test. Serious adverse event rates will be presented by treatment arm and grade. Quality of life scores will be compared using a hierarchical linear regression model.

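### Kaplan–Meier curves for time to first SBP overstate its absolute risk when 23–34% of patients are expected to die by 18 months; cumulative incidence with death as a competing event should replace them

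*Protocol article*

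**What the plan says.** Time to first SBP is the first secondary outcome listed under Outcomes {12}. For its analysis, Statistical methods {20a} says: "Time to the first incidence of SBP will be presented with Kaplan–Meier curves and compared between the arms using the log-rank test". For the other event outcomes the same section says: "Binary secondary outcomes will be analysed using logistic regression". Outcomes {12} defines many of these as incidence at 18 months: C. difficile diarrhoea, other infections with admission, cirrhosis-related events, transplantation, TIPS and resolution of ascites.

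Sample size {14} gives the expected mortality. For control: "we anticipate 66% survival in the control arm at 18 months". For co-trimoxazole: "In the experimental arm, we expect 77% of patients surviving at 18 months". The article nowhere mentions competing events, or how a patient who dies before SBP or before month 18 enters these analyses.

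**The concern.** Death is common in this trial, is expected to differ between the arms, and rules out a later first SBP. Kaplan–Meier treats a patient censored at death as still able to have SBP afterwards. One minus the curve is therefore the risk in a hypothetical population without death, not the share of patients who will have SBP. SBP is the event the drug is meant to prevent, and readers will take absolute risks and their difference from these curves.

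A related question arises for the 18-month binary outcomes. If co-trimoxazole prolongs life, its patients have longer in which to have any event. An odds ratio alone cannot separate that from an effect of the drug on the event.

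**Working it through.** **The plan's own figures.** Inputs from Sample size {14}: HR 0.62, two-sided 5%, 90% power, 66% control survival at 18 months, exponential survival, uniform accrual over 30 months, follow-up 18 to 48 months, 10% loss (taken as exponential, reaching 10% at month 48).

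- Events, Schoenfeld: 4 × (1.960 + 1.282)² / (ln 0.62)² = 184. Freedman: (1.960 + 1.282)² × (1.62/0.38)² = 191. The stated 187 lies between them.
- Probability of an observed death: 0.507 (control) and 0.359 (active), mean 0.433. 187 / 0.433 = 432, as stated.
- Survival: 0.66^0.62 = 77.3%, consistent with the stated 77%.

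The mortality inputs can therefore be used as they stand.

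**Hazards.** Death, control: m = −ln(0.66)/1.5 = 0.277 per year. Death, active: −ln(0.77)/1.5 = 0.174 per year (0.172 if taken as 0.62 × 0.277). The article gives no SBP rate, so the net SBP risk at 18 months is assumed, over 5–30%. At 15%, h = −ln(0.85)/1.5 = 0.108 per year.

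**Formulas, constant hazards.** 1−KM = 1 − exp(−hT). Cumulative incidence = h/(h+m) × [1 − exp(−(h+m)T)].

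**Same SBP hazard in both arms, 15% net risk:**

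| Time | 1−KM, both arms | Cumulative incidence, control | Cumulative incidence, active |
|---|---|---|---|
| 18 months | 15.0% | 12.3% | 13.2% |
| 48 months | 35.2% | 22.1% | 26.0% |

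(The active figure at 18 months is 13.3% with the 0.172 hazard.)

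**Overstatement, 1−KM divided by cumulative incidence, net risk 5–30%:**

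| Time | Control | Active |
|---|---|---|
| 18 months | 1.21–1.22 | 1.13–1.14 |
| 48 months | 1.52–1.63 | 1.32–1.38 |

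**Effect on the absolute difference at 18 months, 15% net control risk.**

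- SBP hazard ratio 0.7: 1−KM gives 15.00 − 10.75 = 4.25 points in favour of the drug; cumulative incidence gives 12.34 − 9.49 = 2.85.
- SBP hazard ratio 0.5: 15.00 − 7.80 = 7.20 against 12.34 − 6.88 = 5.46.

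**Allowing for deaths that follow SBP.** Let SBP multiply the death hazard by k = 3 to 5, and solve for the pre-SBP death hazard that keeps overall control survival at 66%. For net risks of 5–30% the control factor at 18 months becomes 1.14–1.21.

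**18-month binary outcomes.** Take an event whose hazard the drug does not change, and assume earlier deaths count as non-events. At 10% net risk the proportions are 8.2% and 8.8%, OR 1.08; at 30% they are 24.9% and 26.6%, OR 1.10. Over 5–30% the OR is 1.08–1.10 and the risk difference +0.3 to +1.8 points in the active arm.

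**The case against.** Several stronger readings are tempting, and the documents do not support them.

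- *The SBP analysis makes the drug look worse.* It does not. With equal SBP hazards 1−KM is the same in both arms, and because control is inflated more, the curves widen an apparent benefit. Moving to cumulative incidence narrows it.
- *The log-rank test is invalid.* With deaths censored it compares cause-specific SBP hazards, which is a legitimate question.
- *The 18-month logistic regression is biased.* A patient who dies at month 2 without C. difficile did not have it by month 18. Follow-up is at least 18 months, so apart from losses the crude proportions equal the 18-month cumulative incidences. An OR of 1.08–1.10 is then a real difference in incidence that arises through survival. The article also states no rule for deaths, and such a rule can properly sit in the announced analysis plan.
- *Admission rates will be fitted with logistic or linear regression.* The article assigns those models to binary and continuous outcomes and names none for rates.

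It is also fair to say that the size rests on an assumed SBP rate, that some deaths follow SBP, that the 48-month figures concern only the earliest recruits, and that the odds ratio needs both the full survival benefit and no effect on the event. These limit the size. They do not remove the point about the SBP curves, because that method is named and not left open.

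**Conclusion.** The point holds for the SBP curves. With deaths censored, which is the ordinary use of Kaplan–Meier and is assumed here, they would overstate 18-month SBP risk by roughly a fifth in control and an eighth to a seventh in the active arm, and by more later. The absolute difference is distorted as well. The figures rest on the protocol's own survival expectations, constant hazards and an assumed net SBP risk of 5–30%. Deaths after SBP bring the control factor down to as little as 1.14. The hypothesis test for SBP is unaffected.

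For the 18-month event outcomes the point is one of interpretation: without a cause-specific estimate, longer survival could be misread as harm from the drug. The primary analysis and the sample size are not touched. The change is worth making before the analysis plan is finalised.

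**What to change.** - Replace the SBP Kaplan–Meier curves with Aalen–Johansen cumulative incidence curves. Treat death before SBP as a competing event, and transplantation too where it precludes the event. Report the 18-month difference between arms with its 95% CI.
- Keep the log-rank test and describe it as a comparison of cause-specific hazards. Add a cause-specific Cox hazard ratio for SBP, adjusted for the same factors as the adjusted primary model.
- For the 18-month event outcomes that death precludes, report a cause-specific hazard ratio beside the logistic result, and say in the analysis plan how deaths before month 18 are counted.

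The cost is some wording and a little more analysis work, using event and death dates that the trial's outcomes already require. Reported SBP risks will be slightly lower than the Kaplan–Meier figures.

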### Interim analyses {21b}

There are no planned interim analyses. Regular reports regarding patient safety, death, and SBP events will be prepared for IDMC, who will have untrammelled access to study data in order to ensure participants are not placed at avoidable risk. The IDMC processes are described in a separate charter.

### Methods for additional analyses (e.g. subgroup analyses) {20b}

The results on the primary efficacy outcome will be presented according to the levels of the stratifying variables used in the randomisation process. Interaction terms between each of the variables below and treatment will be added in turn to the primary analysis model to investigate whether the treatment effect differs according to the levels of these factors. We will report the treatment effect estimates in the subgroups and the *p*-value of the interaction tests.

The factors for subgroup analysis are as follows:

Rifaximin prescription at randomisationActive participation on liver transplant list at randomisationGenderAscitic fluid protein count (above or below the cut-off of 2 g/dL)Long-term ascites (ascites persistent for more than 3 months at enrolment)

#### Health economic analysis

We aim to calculate the mean incremental cost per QALY gained from using co-trimoxazole to prevent SBP and improve overall survival in cirrhosis patients. The primary analysis will be a within-trial intention-to-treat analysis. Because an 18-month follow-up is considered enough time to capture all important drivers of the cost-effectiveness of the intervention, no economic modelling will be required. Health-related quality of life will be measured using the EQ-5D-5L, which will be collected at baseline and every 6 months during the 18-month follow-up for each patient. Utility scores will be calculated using UK-specific tariffs [37]. QALYs will be calculated as the area under the curve adjusting for baseline differences and minimisation factors as will be specified in the health economic analysis plan. Cost savings are anticipated to result from the prevention of hospital re-admissions and a reduction in other healthcare resource use. Resource use will be valued from the health and social care services perspective. The data will include hospital admissions (including length of stay and type of ward), cost of co-trimoxazole, day-case visits, any tests undertaken, outpatient attendances, primary care contacts, A&E visits, and concomitant medications. Unit costs will be obtained from publicly available sources such as the British National Formulary [38] and Unit Costs of Health and Social Care [39]. We will report descriptive statistics for all health and social care resource use at 18 months for both arms. 95% confidence intervals for the difference in costs between the two arms will be based on the bootstrapped results adjusting for variables specified in the analysis plan. Bootstrapped results will be also used to report the incremental cost per QALY gained. Cost-effectiveness acceptability curves will be constructed to report the probability that co-trimoxazole is cost-effective compared to placebo for a range of values of the cost-effectiveness threshold recommended by NICE [40].

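### The protocol's claim that 18 months captures all important drivers of cost-effectiveness, so that no modelling is needed, conflicts with its own survival assumptions

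*Protocol article*

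**What the plan says.** The section on health economic analysis in the protocol article sets the aim as the "mean incremental cost per QALY gained from using co-trimoxazole to prevent SBP and improve overall survival in cirrhosis patients". The primary analysis is within-trial and by intention to treat. EQ-5D-5L is "collected at baseline and every 6 months during the 18-month follow-up for each patient", and the resource-use report is "descriptive statistics for all health and social care resource use at 18 months for both arms". The horizon is justified in a single sentence: "an 18-month follow-up is considered enough time to capture all important drivers of the cost-effectiveness of the intervention", and therefore "no economic modelling will be required".

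The sample size section plans for a longer period: "the follow-up time will be 18 months minimum with a maximum potential follow-up of 48 months". It assumes exponential survival, with 66% of controls and 77% of the experimental arm alive at 18 months, and states "we anticipate a hazard ratio (HR) of 0.62". Treatment lasts 18 months (trial design section). The background section describes the harm that an SBP episode does to survival and quality of life as long-term.

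**The concern.** The economic aim names better survival as a benefit. When a treatment prevents deaths, much of its QALY gain is the later life of the people kept alive. At month 18 the plan expects about two thirds of one arm and three quarters of the other to be alive, so the gap between the curves has had little time to turn into life-years. The trial goes on following survival after that point, but the economic analysis does not use it.

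The cost-effectiveness acceptability curve is to be read against NICE thresholds, and the abstract anticipates wide adoption if the trial is positive. A cost per QALY presented as complete, when most of the projected survival gain and all of the survivors' later costs lie outside it, could misinform that decision in either direction.

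**Working it through.** **Inputs** (sample size section unless stated): control survival 66% at 18 months; HR 0.62; exponential survival; uniform recruitment over 30 months; follow-up 18 to 48 months; 10% cumulative loss by the end of the study; two-sided 5% error; 90% power; 1:1 allocation and 18 months of treatment (trial design section).

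**Hazards per month.** Control: λc = −ln(0.66)/18 = 0.02308. Experimental: λe = 0.62 × 0.02308 = 0.01431. Experimental survival at 18 months is then 0.66^0.62 = 77.3%, which matches the stated 77%.

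**The plan's own figure first.** The protocol "calculated that 432 patients will be required to generate 187 events". Schoenfeld's formula gives 184 events and Freedman's 191, and 187 events give 90.5% power by Schoenfeld. For the number of patients, take the loss hazard g = −ln(0.9)/48 and, in each arm, with t = λ + g,

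P(death observed) = (λ/t) × [1 − (e^(−18t) − e^(−48t))/(30t)].

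This gives 0.507 for control and 0.359 for experimental, and 216 × (0.507 + 0.359) = 187.1 events. The stated 432 and 187 reproduce, so these inputs are the model behind the design.

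**Survival gain with a constant HR.** Mean survival to time T is (1 − e^(−λT))/λ.
- To month 18: 15.87 − 14.73 = 1.14 months.
- To month 48: 34.72 − 29.02 = 5.70 months.
- Lifetime (1/λ): 69.87 − 43.32 = 26.55 months.

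**Survival gain if the effect stops at month 18** (an assumption: the control hazard applies in both arms afterwards). The gain is 1.14 + (0.7729 − 0.66) × (1 − e^(−λc(T−18)))/λc.
- To month 48: 1.14 + 0.1129 × 21.65 = 3.58 months.
- Lifetime: 1.14 + 0.1129 × 43.32 = 6.03 months.

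**Average over planned follow-up.** With uniform recruitment, planned follow-up is spread evenly from 18 to 48 months. Averaging the gain over that range gives 3.28 months with a constant HR and 2.50 months if the effect stops (loss to follow-up ignored).

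**Share omitted by an 18-month horizon** = 1 − 1.14/gain:

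| Window | Effect stops at month 18 | Constant HR |
|---|---|---|
| Planned follow-up, averaged | gain 2.50; 54% omitted | gain 3.28; 65% omitted |
| To month 48 | gain 3.58; 68% omitted | gain 5.70; 80% omitted |
| Lifetime | gain 6.03; 81% omitted | gain 26.55; 96% omitted |

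**Sensitivity.** Using the HR implied by 77% against 66% (ln 0.77/ln 0.66 = 0.629) leaves these shares unchanged to the nearest percent for month 48 and lifetime. Discounting at an assumed 3.5% a year, a rate the article does not give, changes the constant-HR figures to 79% at month 48 and 94% over a lifetime, and the stopped-effect lifetime figure to 79%.

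**The case against.** The 18-month window has a sound rationale. It matches the treatment period, the minimum follow-up, the EQ-5D-5L schedule and many of the secondary outcomes. It is also the longest period planned for every participant, so it avoids administrative censoring of costs and QALYs. This stands, and it is why the within-trial analysis should stay. It does not support the claim that nothing important happens later.

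The article also refers to a separate health economic analysis plan, which is not shown, and calls the within-trial analysis only the primary one. That carries little weight: the article fixes the horizon and rules out modelling itself, so a plan that added extrapolation would contradict it.

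A reader might infer three stronger things that the documents do not support:
- That the horizon discards 96% of a lifetime gain on which the trial is powered. The power calculation rests on deaths within 18 to 48 months, and no lifetime gain enters it. The 96% needs HR 0.62 to persist for life after 18 months of treatment, while the section on choice of comparators leaves waning of efficacy open.
- That 80% of the gain within the trial's follow-up is lost. Forty-eight months is the maximum, reached only by the earliest recruits; averaged over planned follow-up the share is 54-65%.
- That the cost per QALY is biased against co-trimoxazole. The calculation contains no costs or utilities. Survivors' later costs are omitted too, and they push the ratio the other way. The discussion section describes this population as having many complications and admissions.

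**Conclusion.** The justification is wrong as written. On the assumptions used to size the trial, more than half of the mean survival gain falls after month 18 in every scenario computed: 54-65% over the planned follow-up, 68-80% to month 48 and 81-96% over a lifetime.

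These shares rest on exponential survival and on the planned effect being real. They are life-months, not quality-adjusted. The two scenarios do not cover a treated-arm hazard that rises above control after treatment stops, which would lower the shares.

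The 18-month cost per QALY is therefore a valid but incomplete result, and the direction of its error is not determined. The point should be corrected; it does not affect the primary survival analysis.

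**What to change.** Delete the sentence saying that 18 months is enough and that modelling is not required. Keep the 18-month within-trial analysis and describe it as such.

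Pre-specify in the health economic analysis plan a lifetime secondary analysis that:
- uses the trial's survival data to the end of follow-up and extrapolates beyond it with parametric curves;
- is run under a persisting treatment effect and under no effect after month 18;
- includes sensitivity analyses on utilities and costs after month 18. Simply carrying the month-18 values forward assumes stability in a progressive disease, and varying the treatment effect alone does not test that.

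The survival data are already being collected, and extra EQ-5D-5L visits after month 18 are not needed. The cost is a modest amount of health-economist time and added model uncertainty, which the two scenarios and the sensitivity analyses make visible.

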### Methods in analysis to handle protocol non-adherence and any statistical methods to handle missing data {20c}

The primary analysis will be conducted with the intention to treat principle, without imputation. We will undertake supportive analyses to consider the potential effects of missing data on the primary objective, using threshold analysis (where intervention group subjects who are missing are considered to have died the day after their last contact, and similarly control group subjects will be censored on the day after their last contact).

### Plans to give access to the full protocol, participant-level data, and statistical code {31c}

Enquiries may be addressed to [contact].

### Oversight and monitoring

#### Composition of the coordinating centre and trial steering committee {5d}

Trial oversight is delegated by the trial sponsor, UCL, to the UCL Comprehensive Clinical Trials Unit (CCTU). The trial team assists with the trial design, coordination and day-to-day operational issues in the management of the trial. The Trial Management Group (TMG) assists with the design, coordination, and strategic management of the trial. The TMG is composed of the CI, expert clinicians (hepatologists, microbiologists), PIs, clinical project managers, trial managers, statisticians, data managers, and health economists.

The Independent Trial Steering Committee (TSC) is responsible for the oversight of the trial to safeguard the interests of trial patients. The TSC is composed of independent expert clinicians, independent members and patient representatives, non-independent member clinicians, and observers.

